*Abbreviations*: *AI* artificial intelligence, *ASC* academic self-concept, *SE-12* self-efficacy questionnaire, *SE-12 G* German self-efficacy questionnaire

^a^The nonrandomised control condition (Cluster Type C) completes the same measures as the control condition in the randomised Cluster Types

The primary outcome is the change in communication skills from baseline, measured using a set of questions designed to reflect the communication skills emphasised in the training. This outcome will be assessed at two time points: t0 (baseline, before the start of training phase) and t1 (end of seminar, after training phase). The primary outcome will be analysed as a z-standardised change score to evaluate the improvement from baseline to subsequent time points. We use data collected during a study pilot phase during winter-term 2024/25, to pilot the set of questions and adapt the assessment if necessary.

Secondary outcomes include measures related to the participants of the course, the use of AI and the perceived quality of the course, such as attitudes towards AI, self-concept and self-efficacy, motivation, user experience with the AI tool, as well as students’ evaluations and feedback. These outcomes are assessed at various time points throughout the course using a combination of validated scales and self-developed measures, as detailed in Table 1.

Each student’s interaction with the AI-system is recorded and can be analysed using criteria derived from motivational interviewing best practices (Motivational Interviewing Treatment Integrity, MITI, 4.2) [32] by human raters and AI. These assessments focus on the accuracy and appropriateness of the techniques used.

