### Participants, recruitment, randomisation procedures, and sample size estimates

Recruitment for this study will target students enrolled in the communication skill seminar (*Seminar Gesprächsführung*) as part of the Bachelor of Science in Psychology program at a German university.

Inclusion criteria for study participants are as follows: 1) Being enrolled as student in the communication skill seminar (Seminar *Gesprächsführung*, A3), which is part of the Bachelor of Science in Psychology program; 2) Participating in one of the seminars from summer-term 2025 up to winter-term 2025/2026; 3) At least 18 years of age; 4) Sufficient proficiency in the German language to participate (as the seminar is conducted in German, this is implicitly given, as German language proficiency is required for course participation). There are no additional exclusion criteria for this study.

Recruitment for the main study begins summer-term 2025 up to winter-term 2025/2026. Participants will be informed about the study by the seminar teachers. Students will be encouraged to participate voluntarily, with informed consent required for enrolment. Reminder messages will be sent out to maintain interest and promote participation throughout the study duration.

The timeline for participant enrolment, interventions, and assessments is as follows: Enrolment begins early during each semester/course, where students provide informed consent. We provide the current informed consent forms (for classes randomised to Conditions 1 and 2 and one for classes in Condition 3) as additional file 1. Allocation occurs at the start of the course (t0), followed by the baseline assessments. The end of the course (t1) includes final assessments. Data close-out for each semester occurs after t1 with optional group discussions. Final data close-out will occur following the last semester during which new data are collected, and any follow-up assessments are completed.

With regard to target sample size, our goal is to enrol at least 50 participants per condition to ensure robust statistical power for detecting medium effect sizes, allow stratified analyses, and to enhance the generalisability of our findings. During the two semesters contributing to the main study, we anticipate recruiting participants from at least 10 seminars.

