### Allocation concealment/blinding

The blinding strategy for this study includes rater blinding to maintain the integrity of the data and minimise bias. Given the nature of the study, it is not feasible to blind participants to the type of intervention. Raters responsible for evaluating communication skills exercises and correctness of free-text responses will be blinded to the condition to which the participants were assigned. In circumstances where unblinding becomes necessary (e.g., unforeseen technical issues or procedural clarifications), a strict protocol will be followed to disclose the intervention assignment in a controlled manner.

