### Data analyses

Data collection for the main study phase will be used for the main data analyses, which will be conducted once main data collection has terminated.

Descriptive statistics will be used to summarise the baseline characteristics of the study sample, including measures of central tendency (e.g., mean, median) and dispersion (e.g., standard deviation, interquartile range), as appropriate given the distribution of each variable. These summaries will provide an overview of participant demographics and initial conditions across intervention groups.

For the main effect analyses, mixed-effects models will be employed. Between-class comparisons will be made, accounting for clustering at the class level. If indicated, models will include fixed effects for intervention and period, as well as random effects for semester, classes and participants, as appropriate.

Both intent-to-train (ITT) and per-protocol analyses will be conducted to ensure robustness and comprehensive interpretation of the results. The ITT analysis will include all participants as randomised, regardless of adherence to the intervention, while the per-protocol analysis will focus on data related to periods in which the participant completed the exercises as intended.

Appropriate covariates, such as baseline scores and relevant demographic factors, will be included in the models to adjust for potential confounding. Statistical significance will be set at the alpha level 0.05, and results will be reported with 95% confidence intervals to convey the precision of the estimates.

To minimise missing data, we are employing online data collection, which facilitates real-time entry and immediate correction of inconsistencies, enhancing data completeness. Additionally, we are implementing mixed models in our statistical analyses, which effectively handle missing data by using all available data points to estimate model parameters.

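### Classes are allocated before the T0 assessment and students are unblinded, so T0 may be answered with the arm known: a risk to the baseline that a reordered timeline removes

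*Protocol article*

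**What the plan says.** In the Protocol article, the section on participants, recruitment, randomisation and sample size has students consent early in the course and then fixes this order: "Allocation occurs at the start of the course (t0), followed by the baseline assessments". Randomisation is by seminar class and is done by an independent party.

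The section on allocation concealment and blinding states that "it is not feasible to blind participants to the type of intervention". It protects the rating step only: "Raters responsible for evaluating communication skills exercises and correctness of free-text responses will be blinded to the condition".

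The Study outcomes section ties the two measurements to training and not to allocation: "t0 (baseline, before the start of training phase) and t1 (end of seminar, after training phase"). Table 1 lists what both arms complete at T0. The outcome measures among these are the competence test (primary), academic self-concept, self-efficacy and attitude towards AI.

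T0 is used in two ways. Study outcomes says "The primary outcome will be analysed as a z-standardised change score to evaluate the improvement from baseline to subsequent time points", and Data analyses says "Appropriate covariates, such as baseline scores and relevant demographic factors, will be included in the models to adjust for potential confounding".

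**The concern.** Randomisation makes the arms comparable on whatever the assignment cannot influence. A baseline taken before anyone knows the assignment meets that condition. A baseline taken after students have learned it may not. A student who knows that the class will get the AI tool, or will not, may put more or less effort into the first test, or may rate confidence and attitude towards AI differently.

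Requiring T0 to precede training rules out an effect of the training itself on T0. It does not rule out an effect of knowing the arm. If there is such an effect, it enters the estimated benefit with the opposite sign, through the subtraction, the covariate, or both.

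This differs from selective consent. Even with identical students in both arms, the T0 means could differ because of the arm, and moving consent alone ahead of the draw would not prevent it. Allocation is by class, so the shift would follow the arm, and a random class effect would not remove it.

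**Working it through.** The protocol states no figure on this point, so there is nothing to reproduce. The check is a derivation with labelled assumptions.

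**Inputs from the Protocol article:** allocation precedes T0; participants are unblinded; the primary outcome is a z-standardised change; baseline scores are covariates; the target is at least 50 participants per condition; alpha is 0.05.

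**Assumptions, not in the documents:** an arm-induced T0 shift d0 of 0.1 to 0.3 SD in absolute value, in either direction; a T0-T1 correlation rho of 0.3 to 0.7; equal SDs of 1 at both times; no effect of the shift on T1.

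**Model.** Let A = 1 for the AI arm, U the undisturbed baseline and t the true effect. Then Y0 = U + d0*A and Y1 = rho*U + t*A + error, with the error SD equal to sqrt(1 - rho^2).

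- Raw change: the arm contrast of Y1 - Y0 is t - d0, so the bias is -d0.
- z-standardised change: the SD of change within arm is sqrt(2(1 - rho)), so the bias is -d0/sqrt(2(1 - rho)).
- Baseline-adjusted: the slope on Y0 is rho, so the arm coefficient is t - rho*d0 and the bias is -rho*d0. It is the same whether Y1 or Y1 - Y0 is the response, because Y0 is in the model.

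**Results** (absolute bias; the sign is opposite to that of d0):

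| rho | Size of d0 | Raw change | z-change | Adjusted, raw SD |
|---|---|---|---|---|
| 0.3 | 0.1 / 0.2 / 0.3 | 0.10 / 0.20 / 0.30 | 0.085 / 0.169 / 0.254 | 0.03 / 0.06 / 0.09 |
| 0.5 | 0.1 / 0.2 / 0.3 | 0.10 / 0.20 / 0.30 | 0.10 / 0.20 / 0.30 | 0.05 / 0.10 / 0.15 |
| 0.7 | 0.1 / 0.2 / 0.3 | 0.10 / 0.20 / 0.30 | 0.129 / 0.258 / 0.387 | 0.07 / 0.14 / 0.21 |

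If the response is the z-change and baseline is also a covariate, the last column is divided by sqrt(2(1 - rho)). For d0 of 0.2 this gives 0.06/1.183 = 0.05 at rho 0.3 and 0.14/0.775 = 0.18 at rho 0.7.

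**Simulation check** (400,000 subjects, rho 0.5, d0 = -0.2, true effect zero): 0.199 for change, 0.099 adjusted for baseline, and -0.001 for T1 alone. These agree with the formulas.

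**Effect on the test**, with 50 per arm, rho 0.5, d0 = -0.2 and clustering ignored. For change, the bias divided by its standard error is 0.2/(1 x sqrt(2/50)) = 1.0, and the two-sided false-positive rate is about 17%. After adjustment the ratio is 0.1/(0.866 x 0.2) = 0.58 and the rate is about 9%. The nominal rate is 5%. Allowing for clustering would widen the standard errors and lower both rates. A shift in the other direction would mask a true effect by the same amount.

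**With T0 completed before the condition is drawn or disclosed,** d0 is zero by design and every bias in the table is zero. The sample size does not change.

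**The case against.** The strongest objection is that drawing the allocation before T0 does no harm by itself; only knowledge of the arm at T0 does. A reader might infer from the stated order that students know their arm at T0 and that the change contrast is therefore biased. The documents do not support that. No section says that students or teachers are told before T0, and a draw by an independent party is compatible with later disclosure. The article is also condensed, and the release of the result may be described elsewhere. This stands, and it makes the point a risk. It does not dispose of it: the allocation-then-baseline order is stated text, the AI condition runs for the whole seminar and so must be known near its start, and nothing in the article closes the gap.

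Second, the magnitudes are assumed. A reader might take the 0.30 SD entry as a loss of 60% of a medium effect (0.30/0.50). That combines the largest assumed shift with an unadjusted raw-SD contrast and a value of 0.5 that the protocol never gives, whereas baseline scores are planned covariates. That reading should not be used.

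Third, the primary outcome is a competence test, with free-text answers rated blind. Blind rating protects the scoring but not the student's effort at T0, so a narrower route remains. For the self-report scales, the protocol specifies no change score, and hypothesis H2 speaks of higher levels. There T0 enters at most as a covariate, and only the smaller -rho*d0 term applies.

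**Conclusion.** The point holds as a risk created by the stated sequence, not as a demonstrated bias. Its size depends on two quantities that the documents do not give. Over the assumed ranges (d0 of 0.1 to 0.3 SD, rho of 0.3 to 0.7), the bias would be 0.03 to 0.21 SD with baseline adjustment and 0.085 to 0.387 on the unadjusted z-change scale, in an unknown direction. It rests on the arm being known at T0 and on the T0 shift not carrying over to T1; a shift that persisted to T1 would partly cancel in the change.

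Exposure is greatest for attitude towards AI, because the allocation concerns the very thing being rated. It is smaller for the competence test. Adjustment reduces the bias but does not remove it, and a later analysis plan cannot restore a T0 answered with the arm known. The order of procedures is therefore the place to correct it.

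**What to change.** Change the enrolment timeline so that each class completes consent and the online T0 survey before its condition is drawn. If the independent party draws earlier, state that the result is withheld from students and the teacher until that class's T0 has closed. Release the HAWKI access and instructions only after that.

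One detail follows from the balance rule: if an instructor teaches two randomised classes in a semester, knowing one class's arm reveals the other's, so both results should be held until both T0 surveys have closed.

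A T0 completed after disclosure should be flagged and kept, not discarded: setting it to missing would leave the change score undefined for that student and would sit badly with the planned intent-to-train analysis. Examine such records in a sensitivity analysis, for example comparing T1 without the T0 score.

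The cost is a sentence or two in the timeline and a short delay before the AI exercises start. T0 is part of a data collection that already runs mostly online, and the sample size is unaffected.

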Randomisation for the study will be conducted at the seminar level, with each seminar class being randomised according to the scheme outlined in Fig. 1. The randomisation process will be conducted by an independent party to ensure unbiased allocation, using coin-flip or computer-generated randomisation procedures, to determine to which condition (Condition 1 or Condition 2; Cluster Types A and B, respectively) each class is assigned, while a rule is implemented so that, if a given instructor teaches multiple classes in one semester, the difference in the number of classes assigned to Cluster Type A vs. Cluster Type B does not exceed one. Our main comparison focuses on the randomised arms (Cluster Types A and B). Additional non-randomised comparison classes (Condition 3, Cluster Type C) will be included only if a given seminar cannot be randomised due to scheduling or instructor constraints. These observational data serve as ancillary information but will not be part of the main randomisation-based analysis.

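### The stated minimum of 50 students per condition does not ensure robust power for a medium effect when about ten classes are the randomised units

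*Protocol article*

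**What the plan says.** The section on participants, recruitment, randomisation and sample size states: "our goal is to enrol at least 50 participants per condition to ensure robust statistical power for detecting medium effect sizes, allow stratified analyses". It continues: "During the two semesters contributing to the main study, we anticipate recruiting participants from at least 10 seminars". The same section says "Randomisation for the study will be conducted at the seminar level", and Data analyses says "Between-class comparisons will be made, accounting for clustering at the class level". For the test itself, Data analyses gives: "Statistical significance will be set at the alpha level 0.05, and results will be reported with 95% confidence intervals". Study outcomes defines the scale: "The primary outcome will be analysed as a z-standardised change score". Data analyses also plans to adjust for baseline scores.

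The article puts no number on a medium effect or on robust power, and it gives no ICC, class size or baseline correlation. It does not say whether the 10 seminars are all randomised or may include the non-randomised Type C classes, which are kept out of the main analysis.

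**The concern.** The target counts students, while the design randomises classes and the analysis compares them. Students in one class tend to resemble each other; the Study design section itself cites shared materials and peer discussion as the reason for randomising classes. Two things then reduce power below what 50 independent students per arm would give: the design effect, and the small number of classes available to estimate between-class variation.

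The sentence is a positive assurance about the primary hypothesis (H1), not a detail deferred to another document. If H1 is not confirmed, readers will set the result against a published assurance of robust power and may conclude that a medium effect has been ruled out, when the trial at its stated minimum could easily have missed one. The same sentence also presents the sample as large enough for stratified analyses.

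**Working it through.** **Inputs from the article.** 50 per condition (minimum); 10 seminars (minimum), so at best about 5 per randomised arm; alpha 0.05, taken as two-sided because 95% confidence intervals are reported; z-standardised change score, so SD = 1.

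**Assumptions, because the article gives no figures.** Medium effect d = 0.5 in SDs of the change score; robust power means at least 80%; equal classes of 50/5 = 10; ICC 0.02 to 0.10; baseline correlation r = 0 (unadjusted) or 0.5; no dropout.

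**Step 1: the article's figure under individual randomisation.**
- n per arm for 80% power = 2 × (1.960 + 0.842)² / 0.5² = 62.8, so 63 (64 with the t distribution), not 50.
- At 50 per arm, SE = √(2/50) = 0.200 and the noncentrality is 0.5/0.200 = 2.50. With 98 df, power is 69.7%.
- With baseline adjustment at r = 0.5 the remaining variance fraction is 0.75, SE = √(2 × 0.75/50) = 0.173, noncentrality 2.89, power 81.6%.
- With the normal approximation, 50 per arm is what one-sided 5% with 80% power, or two-sided 5% with 70% power, would return. The article states neither.

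**Step 2: classes as the unit.**
- Design effect DE = 1 + (10 − 1) × ICC.
- SE = √(2 × v × DE / 50), with v = 1 unadjusted and v = 0.75 adjusted (reduction assumed equal at class and student level).
- df = 10 − 2 = 8, critical t = 2.306, noncentrality = 0.5/SE, power from the noncentral t.

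| ICC | DE | SE, v = 1 | Power, v = 1 | Detectable at 80%, v = 1 | SE, v = 0.75 | Power, v = 0.75 | Detectable at 80%, v = 0.75 |
|---|---|---|---|---|---|---|---|
| 0.02 | 1.18 | 0.217 | 52.5% | 0.70 SD | 0.188 | 64.5% | 0.60 SD |
| 0.05 | 1.45 | 0.241 | 44.7% | 0.77 SD | 0.209 | 55.8% | 0.67 SD |
| 0.10 | 1.90 | 0.276 | 35.9% | 0.88 SD | 0.239 | 45.3% | 0.76 SD |

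**Step 3: where the loss comes from.** In the adjusted case, power is 81.6% under individual randomisation, 71.6% with 8 df and ICC 0, and 55.8% with 8 df and ICC 0.05. Dropping the small-sample df correction does not rescue the claim: the normal approximation, unadjusted, gives 63%, 55% and 44% at ICC 0.02, 0.05 and 0.10.

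**Step 4: stratified analyses.** Splitting each arm into two equal strata leaves 25 per arm. Power for d = 0.5 within a stratum is about 41% even under individual randomisation without adjustment.

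**The case against.** The strongest reply is that 50 students and 10 seminars are both floors, and that classes of 10 come only from dividing one by the other. This stands. With the same formulas and r = 0.5, 5 versus 5 classes of 20 give 86% at ICC 0.02 and 73% at ICC 0.05; 7 versus 7 classes of 15 (12 df) give 92% and 84%. A reader might infer that the trial as run will be underpowered. The article does not support that; it shows only that the stated minimum does not secure the stated property.

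A reader might also infer that 50 per arm is too few even if students were randomised individually. That holds only without covariates (69.7%). Data analyses plans baseline adjustment, and at r = 0.5 that gives about 82%.

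Nor should a stronger baseline correlation be assumed to close the gap. The outcome is a standardised change score. With equal variances at both time points, adjusting change for baseline leaves a fraction (1 + r)/2 of its variance. This matches the familiar 1 − r² at r = 0.5 (both 0.75), but it rises with r instead of falling. The result depends on r and on the scale of d, so both need stating.

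The planned mixed model accounts for classes, so the analysis is not invalid on this ground. The article is condensed and a fuller calculation may exist elsewhere, so it cannot be said that the planners overlooked clustering, only that the published numbers do not bear out the assurance. The reported confidence intervals also limit misreading of a null result, though they do not correct the claim.

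On Type C, the article includes such classes only where a seminar cannot be randomised, and it predicts no number. Purely as an illustration, if four of ten seminars were Type C and 50 per arm came from 3 versus 3 classes, unadjusted power at ICC 0.05 would be 30%. That case shows why the count needs defining; it is not a forecast.

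**Conclusion.** The concern holds for the stated minimum. With 50 students per randomised arm in 5 + 5 classes, power for d = 0.5 is roughly 36% to 52.5% unadjusted and 45% to 65% after baseline adjustment at r = 0.5, over ICC 0.02 to 0.10. The adjusted trial would have 80% power only for effects of about 0.60 to 0.76 SD. The phrase "robust statistical power for detecting medium effect sizes" is therefore not borne out at the size to which it is attached, mainly because of clustering and the few classes. The size of the shortfall rests on my assumed d, two-sided 5% test, 80% benchmark, ICC range, equal classes of 10 and r = 0.5. The defect is in the sample-size statement, not in the analysis model.

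**What to change.** Replace the assurance with the power or detectable effect at the stated minimum, naming the assumed ICC, number and size of classes, and baseline correlation. For example: *With 50 students per randomised arm in 5 + 5 classes of 10, ICC 0.02–0.10 and baseline correlation 0.5, power for d = 0.5 (in SDs of change, two-sided 5%) is about 45–65%, and the effect detectable with 80% power is about 0.60–0.76 SD.* If the investigators have their own ICC, class sizes or correlation, those should replace mine.

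State that the 50 per condition and the 10 seminars refer to Types A and B only. Describe stratified analyses as exploratory, not as supported by this sample size.

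The cost is a change of protocol wording and a less favourable stated power. Enrolment, randomisation and the analysis model stay as they are.

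### Coin-flip allocation of about 10 classes, balanced only within one instructor's same-semester classes, leaves an avoidable risk of unequal arms and of missing 50 participants in one arm

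*Protocol article*

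**What the plan says.** All of this is in the protocol article, section *Participants, recruitment, randomisation procedures, and sample size estimates*.

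- Unit: "Randomisation for the study will be conducted at the seminar level".
- Method: an independent party allocates, "using coin-flip or computer-generated randomisation procedures, to determine to which condition (Condition 1 or Condition 2; Cluster Types A and B, respectively) each class" joins. A coin flip is therefore expressly permitted.
- Restriction, a cap of one on the imbalance: "if a given instructor teaches multiple classes in one semester, the difference in the number of classes assigned to Cluster Type A vs. Cluster Type" (the second type being B). No other restriction and no allocation ratio is stated.
- Target: "our goal is to enrol at least 50 participants per condition to ensure robust statistical power for detecting medium effect sizes".
- Clusters: over two semesters, "we anticipate recruiting participants from at least 10 seminars". Non-randomised Type C classes "will be included only if a given seminar cannot be randomised due to scheduling or instructor constraints". The article does not say how many of the 10 or more seminars will be randomised.

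Class size and the number of classes per instructor are not given. The section *Data analyses* plans mixed models that account for clustering by class, with a random effect for semester where appropriate.

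**The concern.** The authors saw a need for balance but built it in at one level only. An instructor with a single class in a semester gets an unrestricted flip, and so does the odd class of any instructor with three or five. An instructor who teaches one class in each of the two semesters gets two independent flips. Nothing ties these flips together.

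With about ten clusters, independent flips often give uneven arms. Three things follow. Precision falls for the same total enrolment. The target, which is stated per arm, can be missed in one arm although the total is ample. And an uneven split inside a semester weakens the within-semester comparison and can leave the AI arm concentrated in one semester.

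**Working it through.** **Inputs.** From the article: 10 classes (its lower figure), the instructor rule, and 50 per condition. Assumed, because the article does not give them: all 10 classes are randomised, classes have equal numbers *m* of consenting students (10, 15, 20 or 25), and several instructor loads. The target of 50 comes with no numerical inputs, so I take it as given. Note that 2 × 50 / 10 = 10 students per class is enough only at an exact 5:5 split.

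**1. Distribution of the split.** Under the rule, an instructor with an even number of classes in a semester contributes a difference of 0 between arms. One with an odd number contributes +1 or −1 with equal probability. If *k* instructor-semesters have an odd count, the A-minus-B difference is a sum of *k* independent ±1 terms. A 7:3 split is a difference of 4, so it needs *k* ≥ 4.

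- *k* = 0 (for example five pairs): always 5:5.
- *k* = 2 (for example 3+3+2+2): 6:4 with probability 0.50, never worse.
- *k* = 4 (three pairs, four singles): P(7:3) = 2 × 1/16 = 0.125.
- *k* = 6 (two pairs, six singles): P(7:3 or worse) = 2 × (1+6)/64 = 0.219; P(8:2) = 2/64 = 0.031.
- *k* = 10 (all singles): P(5:5) = 252/1024 = 0.246; P(7:3 or worse) = 2 × (1+10+45+120)/1024 = 0.344; P(8:2 or worse) = 2 × (1+10+45)/1024 = 0.109; P(9:1 or worse) = 2 × (1+10)/1024 = 0.021.

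**2. Chance that one arm has fewer than 50.** The smaller arm needs (number of classes) × *m* ≥ 50. With *m* = 10 it needs 5 classes, with 15 it needs 4, with 20 it needs 3, with 25 it needs 2.

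| Instructor load | m = 10 | m = 15 | m = 20 | m = 25 |
|---|---|---|---|---|
| Five pairs | 0% | 0% | 0% | 0% |
| 3+3+2+2 | 50% | 0% | 0% | 0% |
| Three pairs, four singles | 62.5% | 12.5% | 0% | 0% |
| Two pairs, six singles | 69% | 22% | 3% | 0% |
| All singles | 75% | 34% | 11% | 2% |

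**3. Precision.** With equal class sizes the standard error is proportional to √(1/a + 1/b) for a and b classes. Relative to 5:5:

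- 7:3: √[(1/7 + 1/3)/(2/5)] = √1.190 = 1.09
- 8:2: √[(1/8 + 1/2)/(2/5)] = √1.5625 = 1.25

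As an illustration of power, take an assumed standardised effect of 0.5, *m* = 15, an intraclass correlation of 0.05 and a two-sided 5% class-level t-test with 8 degrees of freedom. The variance of a class mean is (1 + 14 × 0.05)/15 = 0.113. Power is 0.54 at 5:5, 0.47 at 7:3 and 0.38 at 8:2.

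**4. Balance within a semester, assuming 5 + 5 classes.**

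- All singles: P(4:1 or worse) = 2 × (1+5)/32 = 0.375 per semester; in at least one semester 1 − 0.625² = 0.61.
- One pair and three singles: 2/8 = 0.25 per semester; 1 − 0.75² = 0.44.
- Two pairs and one single: 0.

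**5. After the fix.** With 10 classes, an overall difference of at most one means exactly 5:5, so 7:3 or worse has probability 0. The instructor rule can always be met as well, because odd classes can be offset against each other across instructors and semesters. Ten students per class then just reaches 50 in each arm.

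**The case against.** Several points on the other side have force.

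*Simple randomisation is valid.* Coin flips give an unbiased comparison, and moving from 5:5 to 7:3 costs only about 5 to 7 points of power for 10 to 20 students per class and intraclass correlations of 0 to 0.10. The small number of classes matters more. This stands: the defect is avoidable inefficiency and not bias.

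*The instructor rule may do most of the work.* The authors wrote it for instructors with several classes, so they expect some. If most have an even number, the risk is nil or small. This also stands, and is why the result is a range. More than 10 randomised classes would lower the risk; loss of classes to Type C would raise it.

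*Further restriction may exist elsewhere.* The article refers to a scheme in Fig. 1, which was not available here; computer-generated allocation could be blocked; and a condensed article may omit such detail. But the caption of Fig. 1 mentions no blocking, and the text names both the method and its one restriction while leaving the coin flip open. This is a stated procedure, not silence.

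Two stronger readings do not hold. A reader might infer that arm becomes confounded with AI model version, since *AI implementation and monitoring* expects version changes during the study. Under *Study design*, however, Condition 2 gets no specific access to the AI tools, so version varies only inside the AI arm. A reader might also infer that an uneven split puts 50 per condition out of reach whatever the enrolment. The table contradicts this: even with all singles, the risk falls to about 2% at 25 students per class. Nor is a 4:1 semester fully confounded with arm, since both arms are still present and semester can be modelled.

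**Conclusion.** The concern holds as one of avoidable risk. As written, the procedure permits allocation with no balance across instructors, within semesters or overall, while the recruitment goal is per condition. For 10 randomised classes the chance of a 7:3 or worse split is 0% to 34%, depending on an instructor load that the article does not give. Under the least favourable load, the chance of one arm missing 50 is about 75% with 10 consenting students per class and about 2% with 25. The loss of precision is modest at 7:3 and appreciable at 8:2. These figures assume equal class sizes and no loss of classes to Type C. Validity of the comparison is not in question. The change is worth making because it costs almost nothing and the trial has few clusters.

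**What to change.** Remove the coin-flip option and specify computer-generated restricted randomisation by the independent party. Each semester:

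1. List and fix the set of randomisable classes, and settle which classes are Type C, before any allocation is drawn.
2. Allocate all listed classes together, choosing at random among the allocations in which Cluster Types A and B differ by at most one class within the semester and at most one overall, with the instructor rule kept.
3. Keep the running totals from instructors.

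The cost is a short script and a sentence or two in the protocol. There is one small downside. The overall constraint makes the second semester's split partly predictable: with 5 + 5 classes, a first semester of 3:2 forces 2:3 in the second, although which class goes where stays random. Steps 1 and 3 are there so that this knowledge cannot influence which classes leave randomisation. Balancing the number of classes does not balance participants exactly if class sizes differ.
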